#### Outcomes

##### Primary outcome

Therapy homework adherence (THA) is defined as the relative ratio of completed to requested entries that are implemented in the video diary or the paper-and-pencil diary (which can be completed either independently by the children or with parental support) between the treatment sessions and the independent overall rating of the quality of entries within an assessment week.

The entire study comprises 24 appointments for the children. Starting at the second therapy session, therapy homework will be assigned every other session (sessions 2, 4, 6, 8, 10, 12, 14, 16, 18, 20, 22, 24). Accordingly, the patients will work on the therapy homework a total of 12 times.

For each assignment, patients will be asked to complete either the video diary or the self-observation sheet on five consecutive school days. The relative ratio can be calculated by dividing the number of completed entries through the number of requested entries. The results will range from 0 to 1.

The independent overall rating of the quality of the video diary or the paper–pencil-diary entries is rated on a 4-point Likert scale (0 = poor quality, 1 = low quality, 2 = largely good quality, 3 = good quality). The overall quality includes two specific criteria: (a) the relevance of the content (spoken or written) to the questions asked, and (b) the level of detail of the spoken or written answers. This rating is based on a rating manual specifying the two quality criteria. Five independent raters will rate the video diary and the paper–pencil diary entries. Interrater agreement will be calculated by conducting intraclass correlation (ICC), using a two-way mixed model for consistency and absolute agreement.

In a preliminary analysis of 15 video diary entries, interrater reliability for five independent raters was conducted. The values for consistency were found to be in the “very good” (0.95) range and the values for absolute agreement were found to be in the “average” (0.73) and “good” (0.87) range [60].

The number of completed entries implemented in the video diary or the paper-and-pencil diary and the overall rating of the quality is assessed trough the newly developed Adherence Questionnaire, which is completed by the therapists after every therapy session, but especially in every session that follows a therapy homework week. For example, when therapy homework is assigned in session 2, the therapist will evaluate the results in session 3.

For the Primary Outcome, we use both aspects of THA described above and thus include quantitative and qualitative features. To determine a THA Score we calculate the product of the relative ratio (e.g. three completed entries with five required entries (3/5 = 0.6) and the overall quality score (e.g. 2). The THA Score ranges between 0 and 3.

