### Allocation

Participants will be randomly assigned to either the treatment condition including the AUTHARK app [56] (*n* = 35) or the active control condition, which includes treatment without the AUTHARK app but with paper-and-pencil homework assignments (*n* = 35). We will use computerized block randomization with a block size of 4 and random selections from all 6 permutations. Allocation will only take place after the participants have completed the initial screening, fulfilled all the inclusion criteria and gave their written consent (patients, parents and teachers). The participants will be randomized by the Principal Investigator [name]. The staff members who are also responsible for the recruitment and the initial diagnostics will request randomization. In return, [name] will send a digital answer form to the same staff member, containing the group allocation (experimental or control group). The staff member will then inform the therapist and the family about the treatment intervention.

Due to the nature of the intervention, it will not be possible to blind trial participants, parents/caregivers, and therapists to allocation. However, the parents/caregivers and patients will be blind regarding the specific hypotheses.

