#### Participant timeline

The individual study duration per patient is between five and seven months. Measurements will take place according to a specific schedule. The trial consists of three general parts: a screening process, the intervention period, and the follow-up assessment. Through an initial investigation using standardized telephone screening, a broad assessment of the inclusion and exclusion criteria will be conducted. Shortly after this initial investigation, the pre-treatment measurement (T1) will occur, which involves a detailed examination of the inclusion and exclusion criteria. After being randomized to the experimental or control group, all patients will undergo a first treatment phase (1), consisting of eight patient sessions and two to three parent/caregiver sessions, followed by an intermediate assessment (T2). Subsequently, another treatment phase (2) will be carried out, followed by a main assessment (T3). Non-responders to the treatment (significant symptoms of OD/CDD at T3 based on the clinician-rated parent interview (ILF-EXTERNAL) [53] and on the parent rating (SCL-DBD) from the DISYPS-III [43]) will participate in a third treatment phase (3), followed by a final assessment (T4). Responders to the treatment (no significant symptoms of ODD/CD at T3) will terminate the study and take part in a first follow-up assessment (T3) eight weeks after their last session. After one year, every family will be asked to complete a follow-up survey (T5).

Therefore, four study visits (T1-T4) will take place for all children and parents/caregivers in order to complete assessments. Additionally, there will be 16 study visits for all children and four to six study visits for all parents/caregivers (treatment phases 1 and 2). Within the group of non-responders after T3, there will be a further eight visits for children and two to three visits for parents/caregivers (treatment phase 3).

At the main assessment points (T1, T3/T4), the primary outcome (THA) and the secondary outcomes will be assessed. At the intermediate assessment (T2), the primary outcome and symptoms of ODD/CD as well as comorbid conditions will be assessed using only parent- and child-report questionnaires and without a clinical interview. The primary outcome will additionally be assessed every two weeks, as the therapist will rate the children’s THA using the Adherence Questionnaire (Fig. 5).

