#### Data management and confidentiality

Most of the trial data will be assessed electronically through an online survey tool (LimeSurvey) [79]. After the completion of an assessment point, the stored data will be exported from the platform by a designated employee and saved in an encrypted data network. For each assessment point, the data will be organized according to patient-, caregiver-, and teacher ratings (see above).

The primary outcome of the trial, the THA, will be assessed weekly using the Adherence Questionnaire (see above), which will be completed by the therapists in a paper-and-pencil form in both groups. The data will then be re-entered digitally by one designated employee. The data will be regularly reviewed for completeness, consistency, and plausibility by two members of the project. After each assessment week, the data from the AUTHARK smartphone app (video diary, momentary assessment function) will be exported, transferred and saved to an encrypted network, to which only selected project members will have access.

At the beginning of the study, all participants will receive an individual study identification number. Data collected within the study will be anonymized and can only be associated with the patient by the project staff through the study identification number. Legal regulations for data protection will be fulfilled. All participating families and teachers will be informed about their rights in terms of data storage, data protection, and data deletion.

Informed consent will be obtained both in both written and verbal form from patients, parents/caregivers or guardians, and (if applicable) teachers before screening. For detailed information, see Additional file 2: Model written informed consent. All participants will be able to clarify questions about the study with research staff members. To participate in the study, it is required that both the patient and his/her parents/caregivers or guardians give their assent and informed consent. Likewise, teachers must give their informed consent for study participation. Data entry and processing will take place as soon as signed informed consent is available.

This study is designed as a small monocenter pilot study with no external funding, and there will be no external data monitoring or auditing committee, although this will be considered for a subsequent larger trial.

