## Discussion

The AUTHARK study will yield information about the effects of smartphone-augmented CBT on the THA compared to conventional paper-and-pencil assignments completed between therapy sessions for children aged 6–12 years with a diagnosis of ODD/CD.

The study will also explore the role of therapy homework as a possible mediator of treatment outcome. Furthermore, the trial will describe possible effects of app-augmented CBT on the symptoms of ODD / CD, ADHD, and other comorbid behavioral or emotional problems; on individually defined problem behaviors; on triggering and maintaining factors of peer- and adult-related aggression (social cognitive information processing, impulse control, social skills, empathy, adaptive and maladaptive strategies for regulation of emotions, problem solving competences); on the children’s quality of life; on the children’s and parents’/caregivers’ level of psychosocial functioning; and on the parents’/caregivers’ and patients’ satisfaction with the treatment.

Since this study is designed as a pilot study, there are some aspects that may prove challenging during the course of the study. One of these aspects is the young age of the children we plan to include. However, our preliminary experience with children in this age range is that even children aged six to seven years are able to handle the smartphones and the requirements of the app. This experience is also supported by the results of a small pilot study that investigated the use of a language app with kindergarten children. The authors reported that children aged three to five years were able to use the app well with support [81]. Moreover, the effects of age on usability and adherence to the intervention will be analyzed.

Another challenge of the study is the risk of bias regarding the outcome ratings. Although participating families will not be informed about the hypotheses of the study, they may conclude from the information letter that the use of the AUTHARK app is an innovation and is expected to result in higher therapy homework adherence. Likewise, the treating therapists cannot be blinded to the intervention. However, the detailed descriptions of quality criteria, on which the rating is based, (see “15”) may reduce the risk of bias. Moreover, in a subsequent main study, an independent blinded evaluation of therapy homework adherence will be considered.

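### The primary adherence score has two incompatible sources for its quality component: five independent raters and the unblinded treating therapist

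*Protocol article*

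**What the plan says.** All references are to the protocol article.

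The Primary outcome section builds THA from two parts: the ratio of completed to requested diary entries, and "the independent overall rating of the quality of entries within an assessment week". Quality is scored 0 to 3 using a manual with two criteria, relevance and level of detail. "Five independent raters will rate the video diary" and the paper diary entries as well, and intraclass correlations (ICCs) will be calculated. A preliminary check used five raters and 15 video entries.

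Further on, the same section says of the quality component that "the overall rating of the quality is assessed trough the newly developed Adherence Questionnaire, which is completed by the therapists". The number of completed entries is recorded on the same form. The section adds an example: "when therapy homework is assigned in session 2, the therapist will evaluate the results in session 3". The THA score is the product of ratio and quality, with range 0 to 3.

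Other sections bear on who rates:

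- Participant timeline: "The primary outcome will additionally be assessed every two weeks, as the therapist will rate" the children's adherence on that questionnaire.
- Data management and confidentiality: the primary outcome is measured with the questionnaire, which "will be completed by the therapists in a paper-and-pencil form in both groups".
- Allocation: "it will not be possible to blind trial participants, parents/caregivers, and therapists to allocation".
- Discussion: the unblinded treating therapists are listed under risk of bias in the outcome ratings, the detailed quality criteria are offered as mitigation, and "in a subsequent main study, an independent blinded evaluation of therapy homework adherence will be considered".

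**The concern.** A therapist's score and the mean of five independent raters' scores are different measurements. They can differ in level, in variance and in how they respond to knowledge of the arm. If the protocol supports both, two primary endpoints remain available once the data are in.

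The choice matters more here than for most composite scores, because quality is a multiplier. A rater who is systematically kinder to one arm shifts the whole score by an amount proportional to the completion ratio. Under the therapist reading, one unblinded person supplies both factors of the product.

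There is also a consequence for the next trial. The Sample size section says the pilot is meant to estimate the variance of critical outcome parameters for a confirmatory trial. A variance estimate is useful only if it is clear whose ratings produced it.

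**Working it through.** **Step 1: who rates quality?** The protocol states no figure that could be reproduced, so the statements are set side by side.

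| Section | Source of the rating |
|---|---|
| Primary outcome, definition of THA | An independent rating |
| Primary outcome, rating procedure | Five independent raters, both diary types |
| Primary outcome, data collection | Therapist, on the Adherence Questionnaire, for both count and quality |
| Participant timeline | Therapist rates THA (quality not named) |
| Data management and confidentiality | Therapist-completed questionnaire for THA (quality not named) |
| Discussion | Unblinded treating therapists discussed as a risk to the outcome ratings |

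The conflict lies within the Primary outcome section itself. Participant timeline and Data management and confidentiality point to the therapist only because quality is part of THA by definition. No section says which score enters the product, and none says how five scores would be combined.

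**Step 2: how does a rating bias enter the score?** Let *r* be the completion ratio, *q* the quality rating, and *b* a constant excess given to one arm.

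- THA = *r* × *q*. The protocol's own example gives 3/5 × 2 = 1.2, and the maximum is 1 × 3 = 3, which agrees with the stated range.
- With bias, THA = *r* × (*q* + *b*), so the mean shift is *b* × mean *r*. This ignores truncation at the top of the 0–3 scale, which would reduce it.

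**Step 3: an illustration of size.** Inputs:

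- *b* = 0.25 quality points: assumed, not in the protocol.
- Mean *r* = 0.65 to 0.828: completion rates that the Background section reports for a mood-diary study and an anxiety app. They come from other apps and other populations.
- SD of THA = 0.6 to 1.0, with one THA value per child: assumed, not in the protocol.
- Comparator: the effect of about d = 0.4 assumed in the Sample size section.

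Results:

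- Shift: 0.25 × 0.65 = 0.163, and 0.25 × 0.828 = 0.207.
- Smallest standardised shift: 0.163 / 1.0 = 0.16.
- Largest standardised shift: 0.207 / 0.6 = 0.345, about 0.35.
- Relative to 0.4: 0.163 / 0.4 = 41% and 0.345 / 0.4 = 86%.

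Read the other way, the leniency that would produce d = 0.4 with no true effect is 0.4 × SD / *r*. This runs from 0.4 × 0.6 / 0.828 = 0.29 to 0.4 × 1.0 / 0.65 = 0.62 points on the 0–3 scale.

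**Step 4: does the reliability evidence cover the score used?** The preliminary ICCs come from five raters and 15 video entries. They describe neither the therapist's rating nor paper entries, so if the therapist's score is the endpoint, the reported agreement belongs to a different set of raters.

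**The case against.** **The raters may serve only as a reliability check.** The sentence on the five raters is followed at once by the ICC plan and the preliminary analysis. With the therapist's score as the endpoint, Participant timeline, Data management and confidentiality, and the Discussion would all fit. This is the best reconciling reading, but it does not fit the word independent in the definition of THA, or the unrestricted statement that the raters will rate both kinds of diary. Nor can the therapist easily be read as merely copying down the raters' scores, because the text has the therapist rate and evaluate.

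**The bias is disclosed and this is a pilot.** Both are true. Allocation and the Discussion state that therapists are unblinded, and the Discussion names mitigation. Quantity and quality are also analysed separately as secondary outcomes, so a difference driven by quality would be visible, and the exported app data allow the counts in the app arm to be checked. What stands is that disclosure does not settle whose rating is primary.

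**Stronger readings that a reader might infer, and which the protocol does not support:**

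- That the trial defers all independent rating to a later study. The Discussion defers only an independent *blinded* evaluation, which is compatible with independent unblinded raters now.
- That therapists know the hypotheses. Allocation says only that parents and patients are blind to them and is silent on therapists.
- That a single rater would shrink the true effect by an amount computable from the pilot ICCs. Those ICCs concern quality ratings of video entries. THA also contains a count and is measured at least eight times per child, and the text does not make clear whether the ICCs are single-rater or averaged values.

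**Conclusion.** The point holds as an unresolved contradiction in the definition of the primary endpoint. The Primary outcome section assigns the quality component both to independent raters and to the therapist, and no section decides between them. This conclusion rests on the text alone and needs no assumption.

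The possible bias is conditional. It arises only if the therapist's score is used and therapists rate the arms differently, for which the protocol gives no evidence in either direction. The range of 0.16 to 0.35 for the standardised shift depends on an assumed leniency, an assumed SD and borrowed completion rates. It shows that a modest leniency could be a substantial share of the assumed effect. It is not an estimate of bias in this trial, and undisclosed bias should not be inferred from it.

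**What to change.** Before the primary outcome is analysed:

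1. Define the primary quality component as the mean of the independent raters' manual-based scores, and state how many raters score each assessment week.
2. Use the therapist's Adherence Questionnaire rating of quality as a sensitivity analysis.
3. Reconcile Primary outcome, Participant timeline, Data management and confidentiality, and the Discussion so that all name the same source.
4. Report absolute-agreement ICC separately for video and paper entries, since the preliminary check covered video only.
5. State that raters can infer the arm from the medium.

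**Cost.** No staff are needed beyond the raters already named, but the work is more than editing. All assessment weeks in both arms must be rated. With 70 children and 8 to 12 assignments each, that is 70 × 8 = 560 to 70 × 12 = 840 assessment weeks before dropout. If all five raters score every week, it is 560 × 5 = 2,800 to 840 × 5 = 4,200 ratings. The paper sheets must have been kept; the data management section describes export of the app data but not storage of the sheets. Recruitment began in October 2019 and was due to end in May 2022, so the clarification comes late in the trial and should be dated and reported as such. Independent rating reduces dependence on the treating therapist but does not blind the assessment.

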##### Secondary outcomes

As a secondary Outcome, we will analyze the quantity (relative ratio) and the overall quality rating separately. Additionally, the percentage of tokens received from the therapists for homework compliance will be considered as a secondary outcome measure.

Further secondary outcomes listed below will be assessed at T1 (baseline) and at T3 or T4:Parent-, teacher-, and patient-rated symptoms of ODD/CD, which will be assessed using the respective rating scales: the parent-, teacher-, and patient-rated DISYPS-III Symptom Checklist for Disruptive Behavior Disorder (SCL-DBD parent, SCL-DBD teacher, SCL-DBD patient (ages 11–18)) [43]. Reliability and validity as well as the sensitivity to change of these scales have already been proven in German samples [43].Clinician-rated symptoms of ODD/CD using the Structured Interview for Disruptive Behavior Disorder (ILF-EXTERNAL), which is part of the comprehensive Structured Interview for Children and Adolescents according to ICD-10 and DSM-5 from the DISYPS-Systems (DISYPS-ILF) [53].Overall behavioral and emotional problems assessed using the total score of the German version of the Child Behavior Checklist for ages 6–18 (CBCL/6-18R-total) [44], the total score of the German version of the Teacher’s Report Form for ages 6–18 (TRF/6-18R-total) [45], and the total score of the German version of the Youth Self Report for ages 11–18 (YSR/11-18R-total) [46]. Reliability and validity as well the sensitivity to change of the German versions of these scales have been demonstrated in several studies [44].Triggering and maintaining components of aggressive behavior (social-cognitive information processing, impulse control, social skills, and reactions to the social environment) assessed using the parent- and patient-rated Questionnaire on Aggressive Behavior in Children (FAVK parent, FAVK patient (ages 9–12) [47].Parent-rated satisfaction with the treatment, assessed using the modified German version of the Client Satisfaction Questionnaire (ZUF-8-M parent), and patient-rated satisfaction with the treatment, assessed using the modified German version of the Client Satisfaction Questionnaire (ZUF-8-M patient) [61], which has been shown to be reliable, valid, and sensitive to change [62].

##### Supplementary outcomes

The supplementary outcomes listed below will be measured (pre- and post-treatment) to assess the potential benefit for the main study:Parent-, teacher-, and patient-rated symptoms of ADHD, which will be assessed using the respective rating scales: the parent-, teacher-, and patient-rated DISYPS-III Symptom Checklist for Attention-Deficit/Hyperactivity Disorder (SCL-ADHD parent, SCL-ADHD teacher, SCL-ADHD patient (ages 11–18) [43]. Reliability and validity as well as the sensitivity to change of these scales have already been proven in German samples [43].Individually defined problem behaviors assessed with the parent-rated Individual Problem Checklist (IPC) taken from the THAV manual [4]. The IPC captures four individual parent-defined target problems to be rated on a 6-point Likert-type scale, and has been shown to be reliable, valid, and sensitive to change [63].Patients’ adherence during the weekly therapy sessions (e.g. punctuality, participation in assignments and activities) and parents’/caregivers’ adherence during a parent appointment, assessed using the clinician-rated Adherence Questionnaire [42], which was specifically developed for this trial and is based on items from an already existing questionnaire on treatment adherence which showed good internal consistencies (child: α = 0.90 to α = 0.95; parent: α = 0.88 to α = 0.97) [13].Parents’/caregivers’ adherence regarding possible assignments between the child’s therapy sessions or between the parent/caregiver appointments, assessed using the clinician-rated Adherence Questionnaire (see above).Callous-unemotional traits in children (e.g. lack of empathy) assessed using the parent- and patient-rated German version of the Inventory of Callous-Unemotional Traits (ICU parent, ICU patient (ages 8–12) [48] [49], which has been shown to be reliable, valid, and sensitive to change [64].Problem-solving competences and social information processing assessed using the computer-based Social Problem-Solving Test for children aged 6–12 (SPST), which has been shown to be reliable and valid [7].Strategies for the regulation of emotions assessed using the parent- and patient-rated Questionnaire for the Assessment of Adaptive and Maladaptive Emotion Regulation Strategies (FRUST parent, FRUST patient (ages 8–12) [51], which is based on the German Questionnaire for the Assessment of Emotion Regulation in Children and Adolescents [51].Children’s health-related quality of life measured using the revised parent- and patient-rated Questionnaire for Measuring Health-Related Quality of Life in Children and Adolescents (KINDL-R parent, KINDL-R patient (ages 7–13)) [50], assessing factors regarding the child’s self-esteem, family, friends, physical health, everyday life, and school as aspects of well-being.Parent-rated psychosocial impairment of the child assessed using the modified German version of the Weiss Functional Impairment Rating Scale Parent Report (WFIRS-P-M) [6] (original version: WFIRS-P [65, 66]), which has been shown to be reliable, valid, and sensitive to change [67].Self-reported parental aggression, anxiety, depression, and stress assessed using a modified short version of the German Questionnaire on Parental Aggression (FB-Ä) [68] and the German version of the Depression Anxiety Stress Scale (DASS) [69], which has been shown to be reliable, valid, and sensitive to change [70].
